**Protocol Authorisation:**

**Chief Investigator**: **[name]: _________**

**Sponsor Representative [name] ___________________________ Date: _________**

**Trial Director-[name] ________________________________ Date: _________**

**Independent Chair-[name]: _________**

**Trial Synopsis**

| **Name of Sponsor** | East Kent Hospitals University NHS FoundationTrust |
| --- | --- |
| **Title of the Study** | A randomised, double-blind placebo-controlled trial of Memantine in the treatment of the Agitation in Alzheimer’s Dementia |
| **Trial Acronym** | MAGD – Memantine for AGitation in Dementia |
| **Investigators** | [name] (Principal Investigator); [name], [name] , [name], [name], [name], [name], [name], [name] |
| **Study Centre(s)** | Kent and Medway NHS and Social Care Partnership Trust, Oxleas NHS Foundation trust; Peterborough, Berkshire NHS Mental HealthFoundation trust, Oxford and Buckinghamshire NHS foundation trust; Plymouth |
| **Study Period** | September 2007 to May 2010 |
| **Objectives** | **Primary Objectives:** To determine the efficacy of Memantine in the treatment of acute agitation in Alzheimer’s Dementia.  **Secondary Objectives:** To estimate the overall symptom response rate to Memantine in the trial population. To investigate whether there are any adverse effects of Memantine in this population. |
| **Methodology** | A 6 week placebo controlled RCT of Memantine in AD with a blind extension to 12 weeks . Planned enrolment is 164. Patients and their clinician’s may withdraw from the study because of a clinically significant worsening in their psychiatric symptoms. These cases and those remaining under double-blind conditions will be followed for a total of 12 weeks. This will enable us to i)maximise the safety data on Memantine and ii)facilitate recruitment into the study, while retaining a strict 12 week RCT. |
| **Number of participants** | 164 |
| **Diagnosis and Criteria for Inclusion** | Inclusion criteria:  1. Residential/Inpatients at recruitment to the study with a history of at least 2 weeks behavioural disturbance.  2. Alzheimer’s Disease only as per McKhann Criteria + Haschinski Score<=4.  3. Moderately severe to severe Alzheimer’s Disease (baseline MMSE </=19).  4. Clinically significant agitation that requires treatment.  5. Severity of agitation defined by Cohen Mansfield agitation inventory (CMAI) > /=45.  6. Age >/= 45.  Exclusion criteria:  1. Memantine usage in the 4 weeks prior to the start of the study.  2. On Cholinesterase inhibitor for less than 3 months and not on a stable dose.  3. Anti-psychotic, anti-epileptic, antidepressant, benzodiazepine, lithium or hypnotic dosage alteration in the 2 weeks prior to the start of the study.  4. Antiparkinsonian medication.  5. Hypersensitivity to memantine or any of the excipients in the formulation.  6. Severe renal impairment.  7. Epilepsy, history of convulsions or seizure, or receiving any anti-epileptic treatment.  8. Concomitant usage of N-methyl-D-aspartate (NMDA) antagonists such as amantadine, ketamine or dextromethorphan.  9. Recent myocardial infarction, uncompensated congestive heart failure and uncontrolled hypertension.  10. Severe, unstable or poorly controlled medical illness.  11. Any disability that may interfere with the patient completing the study procedure.  12. Active malignancy.  13. Delirium, pain or any medical illness as a clear cause of agitation..  14. Any important drug interactions: Prohibited during study and in the 14 days preceding enrolment/inclusion are: Analgesic  dextromethorpan, Dopaminergics- amantadine, Warfarin due to theoretical INR prolongation. |
| **Intervention** | Memantine at the following doses; Week 1: 5mg once daily, Week 2: 5mg twice daily, Week 3: 5mg morning and 10mg at night. Week 4: 10mg twice daily If patient responding and with no adverse effects, continue with this level regime. After week 4, reductions may be made in 5mg steps or greater if indicated and as determined by treating clinicians. |
| **Duration of Intervention** | Up to 12 weeks if no adverse effects / worsening of agitation |
| **Control Intervention** | Placebo tablets. Identical to active drug, tablets given as per active drug titration regime. |
| **Outcome Measures** | **PRIMARY ENDPOINT**:  Change in CMAI at 6 weeks at 10mg twice daily dose – primary hypothesis 5 point difference in change score in favour of memantine. Intermediate assessment points at 2, 4, and 6 weeks.  **SECONDARY ENDPOINTS**:  Neuropsychiatric Inventory (NPI) 6+ 12 weeks, Clinical Global Impression (CGI), Severe Impairment Battery (SIB) at , 6 and 12 weeks, Change in CMAI at week 12, Quality of Life 6+ 12 weeks(QOL-AD), co-prescribed psychotropic medications, number of recorded incidents of aggression, and number of occasions rescue treatment utilised. NPI at 6 and 12 weeks  Respondent:  The difference between the memantine and the placebo groups at 6 weeks in the proportion of patients who are considered respondent. The respondent patient is a patient who had a 50% reduction in their total CMAI score. |
| **Statistical Methods** | The final analysis plan will be determined in consultation with the statistician but will involve the change in agitation inventory score from baseline to 6 weeks using the mean(SD). We may use standard survival analysis for remaining in trial and between-group ANOVA for clinical measures. |
| **Date of Final Version: 6.0 17.06.08** | |

**Randomisation Centre:**

[name] + [name].
[contact]

Micron Research Ltd [name]
[name] United Kingdom

- 1. **Trial Steering Committee (TSC)**

The terms of reference of the MAGD Trial Steering Committee are as follows:

- - - - 1. To approve the final protocol for the MAGD trial. If changes are required to the final protocol, to agree these changes before they are put into effect.
        2. To monitor and supervise recruitment, adherence to the protocol and patient safety, from information provided by the trail management group.
        3. To review reports of serious adverse events or unexpected adverse reactions during the course of the trial.
        4. To endeavour to ensure that the trial is conducted at all times to the rigorous standards set out in the MRC Guidelines for Good Clinical Practice and in line with EU legislation for clinical trials involving medicinal products.

The membership of the TSC is as follows:

[name] Director

[name] Principal Investigator

[name] Co-investigator

[name] Co-Investigator

[name] Co-Investigator

[name] Co-Investigator

Clinical Research Fellow

[name] Northwise Systems

Independent Members:

##### [name]

[name]

[name]

[name] [contact]

The protocol was finalised by the end of July 2006. It is anticipated that targets will be set for recruitment, data collection, compliance etc. to act as a gauge of trial progress and that a set of data will be agreed (based on these targets) to present to the TSC. A draft template used by the MRC is as follows:

|  | **Target**  (Date Target Set) | **Achieved**  (Date Achieved) |
| --- | --- | --- |
| 1. Name of Trial 2. Grant Number 3. Sample Size Sought 4. Date Recruitment Started 5. Proposed Date for Recruitment End 6. Actual Recruitment Rate versus Target Rate (by month / quarter) 7. Acceptance Rate as a proportion of 8. those invited to participate 9. if known all eligible participants 10. Quarterly / monthly forecasts of recruitment for the planned remainder of the trial 11. Losses to follow-up 12. as a proportion of those entered 13. per month / quarter 14. Completeness of data collected 15. Any available results (pooled) 16. Any organisational problems |  |  |

After this it is anticipated that the TSC will be consulted when recruitment has been completed, when data collection and analysis have been completed and when the results will be presented.

- 1. **Data Monitoring Committee (DMC)**

The functions of a Data Monitoring Committee will be performed by the trial management group, according to the terms of reference outlined in the MRC’s Guidelines of Good Clinical Practice (1998)

- 1. **Trial Management Group (TMG)**

A Trial Management Group has been set up to oversee the development of a full protocol for the trial and the day-to-day running/management of the trial. It is anticipated that the TMG will also be responsible for overseeing the writing of trial reports and publications.

[name] Director

[name] Principal Investigator

[name] Co-Investigator

[name] Co-Investigator

[name] Co-Investigator

[name] Co-Investigator

[name] Co-Investigator/Pharmacy Kent [name] Clinical Research Fellow

[name] Co-investigator

The TMG has met by face-to-face/ teleconference/e-mail approximately monthly during the protocol development phase. It is anticipated that once monthly contacts will continue.

- 1. **Staff Training Programme**

All employed staff and all investigators will be trained in:

GCP- mandatory for principal investigators

Use of Assessment procedures

Trial Standard operating procedures

Up-to-date CVs of all staff working on the trial will be kept in the trial office as well as a log of all training received.

- 1. **Declarations of Competing interests**

All investigators have received support from pharmaceutical companies for example to attend conferences, for giving lectures, for provision of consultancy or for the conduct of research.

No investigator or member of staff employed on the grant has any shareholding in any company that might gain form the subject

**3 Protocol Amendments**

The proposal submitted was submitted to the LREC for ethical review. It is referred to as Protocol Version 4.0.

Protocol Version 4.0 has been presented to the Trial Steering Committee and approved. The approved final protocol will be sent to the LREC, Lundbeck Ltd, Kent and Medway NHS and Social Care Partnership Trust and East Kent Hospitals Trust.

Protocol amendments 5,6 were new sites opening-from originally just Kent and Medway NHS and social care partnership trust and Oxleas NHS foundation trust. Protocol version 7 reduced age for inclusion to 45 years.

**4 Background Information**

- 1. **Introduction**

Alzheimer’s disease (AD) is a chronic progressive degenerative disorder of unknown aetiology. Dementia has an estimated prevalence of approximetely 750000 individuals in the UK and Alzheimer’s is the commonest cause of dementia (Wimo et al 2003). Dementia affects one person in 20 aged over 65 years and one person in five over 80 years of age (Jorm et al 1987; Hoffman et al 1991).

AD is characterised by the gradual onset and progressive worsening of cognitive, functional and behavioural symptoms. In the mild stages (Mini-Mental State Examination (MMSE) score of 20-26) symptoms can be subtle and include short term memory loss, impaired activities of daily living and behavioural change (Galasko 1998). In the moderate stage (MMSE 10-19) these deficits are more pronounced and severe. In the severe stage (MMSE<10) the behavioural symptoms are the most prevalent (Mega et al 1996).

Behavioural and psychological symptoms difficulties are part of dementia syndrome and are the commonest reason for placement breakdown and have a significant effect on carer burden (Burns et al 1990; Chan et al 2003; Cohen Mansfield et al 1986; Finkel 1998; Shah 1992). Neuropsychiatric symptoms occur in 80-90% of patients during the course of dementia (Alten et al 2005; Steinberg et al 2004). Incidence rates of agitation in patients with mild-to-moderate AD are 20% to 40% after one year and up to 50% to 60% after two years (Hope et al., 1999). Agitation becomes more common as dementia progresses.

Agitation is classically defined as “inappropriate verbal, vocal or motor activity that is not judged by an outside observer to result directly from the needs or confusion of the person” (Cohen-Mansfield and Billig, 1986b). Agitated behaviours have been divided into three subtypes (Cohen-Mansfield et al., 1995b; Cohen-Mansfield et al., 1989a): aggressive behaviours; physically nonaggressive behaviours, such as pacing; and verbal agitation, such as constant repetition of sentences. Agitation in dementia is unique, however, in that its prevalence is linked with the progression of the dementia itself (Cohen-Mansfield et al., 1995a) and with the unique abilities and disabilities affected by this progression. For example, verbally nonaggressive behaviours are most prevalent in the middle stages of dementia when verbal abilities are still maintained, but the ability to use them effectively is diminished. In contrast, aggressive behaviours tend to occur in late stages of dementia, when verbal communication is severely compromised. Similarly, the quality of the behaviour differs from that of other psychiatric symptoms. For example, aggressive behaviours are usually a response to actions by others, which the older person does not comprehend and does not want. (Cohen-Mansfield et al., 1992; Cohen-Mansfield and Werner, 1995a). Agitation is associated with aggression. Physical aggression is the most common type of aggression (76%) (Astrom *et al*., 2002). In a study in residential institutional setting, Goodridge (1996) found that nursing assistants were verbally assaulted 11.3 times per month and physically assaulted 9.3 times per month. Physical attacks on other persons by patients with Alzheimer’s disease or other dementia’s have been reported in 20% of community-based patients and 50% of those in institutions (Macpherson *et al*., 1994; Webster and Grossberg, 1996; Coen *et al*., 1997).

Agitation is a well-recognised complication of the disease and is a common reason for admission, as well as being highly prevalent in the inpatient setting. It also affects length of stay and has an impact on future care planning.

- 1. **Relevant Studies**

Agitation and its constituents are problematic to manage and in the past overuse of medication has resulted in inappropriate management (Ballard and Cream 2005). Concern has also been raised as many patients end up on long term medication when there is evidence that behavioural disturbances are short lived/ self limiting (IPA, 1998; 2002). Non-pharmacological interventions can assist but again speed of response and overall effectiveness in severe agitation requires further study (Livingston et al 2005). Antipsychotics are generally acknowledged to be more effective than a variety of other pharmacological agents in the treatment of BPSD (APA., 1997). Typical antipsychotics are recognised to be moderately effective and their use has been restricted by their potential serious side effects (Raskin, 1985; Schneider et al 1990; Mcshane et al 1997). Atypical antipsychotics have a lower potential to cause extrapyramidal side effects than typical antipsychotics (Brodaty et al 2003; Suh et al 2004; Street et al 2000; Targum and Arvantis 1997). In March 2004 the committee for safety of medicines recommended that risperidone and olanzapine should not be used to treat behavioural problems associated with dementia because a meta-analysis showed a threefold greater risk of strokes when either drug was prescribed to patients with dementia and a twofold higher mortality with olanzapine (CSM, 2004). Subsequent analyses have confirmed an increased in cerebrovascular adverse events and mortality within 10-12 weeks of treatment (Layton et al 2005; Schneider et al 2005) and that there was little distinction between the atypicals although the issue of risk factors interacting with atypicals remains unresolved (Carson et al 2006; Liperoti et al 2005). There appear to be similar risks with typical antipsychotics (Herrmann and Lanctot 2005; Wang et al 2005). Overall Pharmacological therapies are not particularlyeffective for management of neuropsychiatric symptoms of dementia.Of the agents reviewed, the atypical antipsychotics risperidoneand olanzapine currently have the best evidence for efficacy.However, the effects are modest and further complicated by anincreased risk of stroke. Additional trials of cholinesteraseinhibitors or memantine enrolling patients with high levels of neuropsychiatricsymptoms are warranted (Sink et al 2005).

- 1. **Rationale**

The latest agent to be studied is Memantine and is particularly promising. It is an non-competitive N-methyl D-aspartate (NMDA) receptor antagonist, which blocks the effect of pathologically elevated tonic levels of glutamate that may lead to neuronal dysfunction (Danysz and Parsons 2000). Memantine acts like Magnesium ions at the NMDA receptor preventing background (noise) activation whilst allowing activation for long term potentiation formation (Chen et al 1992; Danysz and Parsons., 2000; Francis 2003). It is currently licensed for Moderately severe to severe AD.

There is a case report of antipsychotic sparing and ultimate stopping when using memantine in disturbed behaviour (Sleeper et al 2005). One RCT published found benefit with agitation at 3 months (Reisberg et al 2003) in secondary outcome measures and unpublished data reports a reduction of 13% in agitation at 6 months (Lundbeck 2005-Data on file). Cummings (2004) reported that memantine in contrast to cholinesterase inhibitors had a pronounced benefit on agitation/aggression. In an analysis of two key trials (Reisberg et al 2003; Tariot et al 2004) a reduction in agitation if present at onset of treatment or a delay in emergence using memantine at 24 and 28 weeks respectively (Gauthier et al 2005) In a pooled analysis of key trials 35% more patient complained agitation on placebo than on Memantine at 6 months (Doody et al 2005). A Cochrane systematic review confirmed this: Patients taking memantine appeared to be less likely to develop agitation (93/1167 [8%] versus 134/1141 [12%] (Peto odds ratio (OR): 0.65, 95% CI 0.49 to 0.86, P = 0.002). This was consistently seen in moderate to severe dementia. There were no data which suggested an effect on agitation which is already present and the effect size was small requiring 25 patients to be treated but further studies are required (Areoasa- Sastre et al 2005). The recent NICE appraisal (NICE 2005) recognised this finding and it preliminary recommendation was that “Memantine should be prescribed only as part of ongoing or new clinical studies that are designed to generate robust and relevant data on long-term outcomes, disease progression through relevant health states, quality of life and costs”. The final ACD from NICE (2006) stated “Memantine is not recommended as a treatment option for people with Alzheimer’s disease except as part of properly constructed trials”.

About 65% of patients with severe Alzheimer's Disease (AD) will have symptoms of agitation (Hope et al 1999). There are drawbacks associated with the currently available therapeutic interventions for agitation associated with Alzheimer's Disease. In a recent trial, in the group of patients with moderate to severe AD treated with memantine, there were fewer incidences of agitation (Doody et al 2005). There is therefore a clear need for shorter scale pragmatic trial in this area to consider the anti-agitation effect of memantine in the acute progressive phase in AD. It is hypothesized that memantine will be effective in reducing the symptoms of agitation associated with moderate to severe Alzheimer's Disease.

- 1. **Risks & Benefits**

Memantine has a favourable safety profile (Alva et al 2005; Doody et al 2005, Livingston and Katona 2005; Reisberg et al 2003). The current medication provision for agitation has a very limited evidence base and is not without morbidity issues for example over-sedation with some antidepressants and falls with antipsychotics. Memantine is a potential treatment with low morbidity even in comparison to the cholinesterase inhibitors. It may offer practical advantages over other drugs but there have been no RCTs which have looked at under 12 weeks.

1. **Objectives & Purpose**
   1. **Primary Objective**

To determine the efficacy of Memantine in the short term treatment of Agitation in Alzheimer’s dementia.

- 1. **Secondary Objectives**

1. To investigate the effect of Memantine on the subtypes of agitation such as verbal and physical aggression plus other sub-groups.
2. To investigate the effect of Memantine on other secondary outcome measures, namely activities of daily living, other BPSD symptoms specifically mood and psychosis, the need for rescue pharmacological intervention such hypnotics and antipsychotics, cognitive functioning**.**
3. To investigate what baseline factors predict clinical response.
4. To investigate whether there are any adverse effects of Memantine treatment in the study population.

5. To investigate the effect of Memantine on quality of life measures.

1. **Trial Design**
   1. **Description of Overall Trial Design and Plan**

A double-blind, randomised placebo controlled trial of Memantine for agitation in Alzheimer’s disease

164 Eligible Consenting subjects with AD and Agitation

Study Group

Randomisation

Baseline assessment

Placebo Group

2 week assessment

6 week assessment

If there is a deteriorating patient;

-Withdraw (without breaking blind)

-or treat clinically rescue alternatives up to week 3 of trial only

Study Group

Rescue Group

Placebo Group

12 week assessment

4 week assessment

- 1. **Selection & Withdrawal of Study Population**

To be eligible for entry into the trial individuals must satisfy **all** of the inclusion criteria and **none** of the exclusion criteria.

**6.2.1 Inclusion Criteria**:

- 1. Residential/In-patients at recruitment to the study with a history of at least 2 weeks behavioural disturbance.
  2. Alzheimer’s Disease only as per NINCDS-ADRDA Criteria (McKhann et al 1984) + Haschinski Score<=4.

3.. Moderate to severe Alzheimer’s Disease (as determined by baseline MMSE < 19).

4. Clinically significant agitation that requires treatment.

5. Severity of agitation defined by Cohen Mansfield agitation inventory (CMAI) ≥ 45 (Cohen Mansfield 1995).

6. Age > 45.

- - 1. **Exclusion Criteria**

1.Memantine usage in the 4 weeks prior to the start of the study.

2. On Cholinesterase inhibitor for less than 3 months and not on a stable dose.

3. Anti-psychotic, antidepressant, benzodiazepine, lithium or hypnotic dosage alteration in the 2 weeks prior to the start of the study.

4. Antiparkinsonian medication.

5. Hypersensitivity to memantine or any of the excipients in the formulation.

6. Severe renal impairment.

7. Epilepsy or history of convulsions or receiving antiepileptic medication.

8. Concomitant usage of N-methyl-D-aspartate (NMDA) antagonists such as amantadine, ketamine or dextromethorphan.

9. Recent myocardial infarction, uncompensated congestive heart failure and uncontrolled hypertension.

10. Severe, unstable or poorly controlled acute or chronic medical illness.

11. Any disability that may interfere with the patient completing the study procedure.

12. Active malignancy.

13. Delirium pain or any medical illness as a clear cause of agitation.

14. Any important drug interactions: Prohibited during study and in the 14 days preceding enrolment/inclusion are: Analgesic dextromethorpan, Dopaminergics- amantadine. Warfarin in due to theoretical INR prolongation.

During the study patients will be allowed to continue taking stable doses of concomitant medicines including antidepressants, antihypertensives, anti-inflammatory drugs, atypical anti-psychotics, anticoagulants, laxatives, diuretics, hypnotics and benzodiazepines (Tariot et al, 2004). Concomitant administration of anti-parkinsonian medication will be permitted but stable dose and no patients on amantadine this is to avoid difficulties with PD stability as Memantine can have benefit in PD. Cholinesterase inhibitors will not be permitted unless patients have been stable on that medication for at least 3 months. The commencement of new psychotropic medications will not be permitted during the study except for rescue treatment as per guidelines (appendix 6) for managing the behavioural symptoms of dementia.

- - 1. **Consent / Assent**

The patient or patient’s legally authorized representative must provides written informed consent (with the patients assent) to participate in the trial

- - 1. **Subject Identification**

Patients assessed for eligibility (*prior to consent / assent for participation in the trial*) will be assigned an **identification number.**

Once randomised into the trial (*post consent / assent for participation into the trial*) a subject will be assigned a **randomisation code.**

- - 1. **Stopping Rules** There are two criteria for removal of subjects from the trial;

1. Unblinding will occur in the event of life-threatening change in physical state or need for urgent medical and/or psychiatric intervention as requested by the patient’s treating physician in consultation with the study team and study monitoring committee.

2. Drop out from the 12 week-phase of the study is permitted due to intolerable side-effects and clinically significant persistent uncontrolled agitation. This will be a primary end point but will not necessitate un-blinding for that patient.

If patients withdraw their consent for follow-up then, if at all possible, the reason for loss to follow-up should be ascertained and permission should be requested to use data collected already for the purposes of the trial. No further data will be collected on patients who withdraw from follow-up. They have the right not to give a reason for withdrawing from follow-up and also to request that no data is held on them.

If patients request that no data is held on them, this should be documented in the patient’s source notes. The source notes should be kept (for audit purposes and to prove the subject existed) but all identifiable details should be blanked out and the data should not be used in the final analysis. It is not anticipated this will be a common occurrence.

- 1. **Pre-Randomisation Assessments & Procedures**

This section describes the assessments and procedures that occur from first contact to randomisation of consenting or assenting eligible patients. A summary of this process is given in Section 6.3.1. Further details are provided in Sections 6.3.2 to 6.3.10.

- - 1. **Flow Diagram of Process**

Links Established with

Old Age Psychiatrists

Patients referred by above groups to MAGD Team

Ineligible patients referred back to original referrer

Eligibility assessment

All Eligible Patients/carers

Provided With Information Sheets

Written Informed Consent

Baseline Assessment

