**Eligibility Assessment**

Name: DOB: Identification no.

Randomisation code: Date at baseline:

Investigator: Centre:

| **Inclusion checklist** | **Y or N** |
| --- | --- |
| Can consent/assent |  |
| Meets Mckann Criteria + Hachinski</=4 |  |
| CMAI>/= 39 |  |
| Agitation considered problematic. |  |
| Symptoms present for >2 weeks |  |
| In patient/Nursing home |  |
| MMSE</=19 |  |
| Age>/=45 |  |
|  |  |

| **Exclusion checklist** | **Y or N** |
| --- | --- |
| Memantine usage in prior 4 weeks |  |
| On Cholinesterase inhibitor for less than 3 months and dose not stable |  |
| Antispsychotic, anti-epileptic, antidepressant, benzodiazepine, lithium, or hypnotic dosage alteration in the 2 weeks prior to the start of study |  |
| Antiparkinsonian medication |  |
| Any contraindication to Memantine |  |
| Hypersensitivity to Memantine |  |
| Severe renal impairment |  |
| Epilepsy, history of convulsions or seizure, or epilepsy, or receiving any anti-epileptic treatment. |  |
| Concomitant usage of NMDA antagonists such as amantadine, ketamine or dextromethorphan |  |
| Concomitant use of Warfarin |  |
| Recent myocardial infarction, uncompensated congestive heart failure and uncontrolled hypertension |  |
| Severe, unstable or poorly controlled medical illness |  |
| Any disability that may interfere with the patient completing the study procedure |  |
| Active Malignancy |  |
| Delirium, pain or any medical illness as a clear cause of agitation. |  |
| Any important drug interactions: Prohibited during study and in the 14 days preceding enrollment/inclusion are: Analgesic dextromethorpan, Dopaminergics- amantadine , Warfarin due to theoretical INR prolongation. |  |

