**Does the patient meet all of the Inclusion Criteria** *(Delete as appropriate)* **YES / NO**

**Does the patient meet any of the Exclusion Criteria** *(Delete as appropriate)* **YES / NO**

**Is the patient Eligible for the MAGD Trial?** *(Delete as appropriate)* **YES / NO**

**BASIC DETAILS**

| Identification number |  |  | Patient Initials |  |
| --- | --- | --- | --- | --- |

| Patient DOB | / / 19 |  | Patient Gender | Female / Male |
| --- | --- | --- | --- | --- |

| **Patient Details** | | | | | | |
| --- | --- | --- | --- | --- | --- | --- |
| Title |  | | | | | |
| Forename |  | | | | | |
| Surname |  | | | | | |
| Address |  | | | | | |
| Ethnicity | White | Mixed | Asian | Black | Chinese | Other |

| **GP Details** | |
| --- | --- |
| Title |  |
| Forename |  |
| Surname |  |
| Address line 1 |  |
| Address line 2 |  |
| Address line 3 |  |
| Town |  |
| County |  |
| Postcode |  |
| Telephone |  |
| Practice/GP code |  |
| PCT code |  |

| **Alzheimer’s Disease Consultant Details** | |
| --- | --- |
| Title |  |
| Forename |  |
| Surname |  |
| Address line 1 |  |
| Address line 2 |  |
| Address line 3 |  |
| Town |  |
| County |  |
| Postcode |  |
| Telephone |  |
| Department |  |
| NHS Trust |  |

| **Relative/Carer Details** | |
| --- | --- |
| Title |  |
| Forename |  |
| Surname |  |
| Address line 1 |  |
| Address line 2 |  |
| Address line 3 |  |
| Town |  |
| County |  |
| Postcode |  |
| Telephone |  |
| Relationship to resident | Spouse / Sibling / Child / Friend / Neighbour / Parent |
| Gender | Female / Male |

| Basic Details Notes |
| --- |

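### The eligibility checklist accepts CMAI scores of 39 or more, while the synopsis and section 6.2.1 both require 45 or more

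*Protocol*

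**What the plan says.** The criteria are stated in full twice. Section 6.2.1 has "Severity of agitation defined by Cohen Mansfield agitation inventory (CMAI) ≥ 45", and the Trial Synopsis has "Severity of agitation defined by Cohen Mansfield agitation inventory (CMAI) > /=45". Section 6.2 gives the rule for applying them: "To be eligible for entry into the trial individuals must satisfy" every inclusion criterion and no exclusion criterion.

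A third statement is the Eligibility Assessment form in Appendix 1. Its inclusion checklist sets the CMAI line at 39 or more. The form closes with a yes/no item, "Is the patient Eligible for the MAGD Trial".

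Smaller differences sit beside this one:

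- **MMSE.** Section 6.2.1 has "as determined by baseline MMSE < 19". The synopsis has "baseline MMSE </=19", and the checklist agrees with the synopsis.
- **Age.** Section 6.2.1 requires more than 45 years. The synopsis and the checklist admit patients aged exactly 45.
- **Need for treatment.** Section 6.2.1 and the synopsis require "Clinically significant agitation that requires treatment". The checklist has "Agitation considered problematic".
- **Duration.** Section 6.2.1 and the synopsis ask for at least 2 weeks of disturbance. The checklist asks for more than 2 weeks.

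**The concern.** The CMAI is both the severity criterion for entry and the primary outcome. The CMAI threshold therefore defines the population whose CMAI change the trial reports. The checklist is a working document: section 6.3.5 has the research fellow or CSO do the screening, and section 7.1 counts eligibility assessments among the source notes. A site that works from the printed form could hold a source record that certifies a patient as eligible when sections 6.2 and 6.2.1 say otherwise. A check of enrolment against that form alone would not reveal the problem.

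At stake is whether all sites recruit to the same definition of clinically relevant agitation, and whether the final report can state one entry threshold truthfully.

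**Working it through.** No sample-size or power figure is involved, so there is no planned figure to reproduce. The check sets the three statements side by side.

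| Criterion | Synopsis | Section 6.2.1 | Appendix 1 checklist | Odd one out |
|---|---|---|---|---|
| CMAI | ≥45 | ≥45 | ≥39 | Checklist |
| MMSE | ≤19 | <19 | ≤19 | Section 6.2.1 |
| Age | ≥45 | >45 | ≥45 | Section 6.2.1 |
| Need for treatment | must require treatment | must require treatment | considered problematic | Checklist |
| Duration | at least 2 weeks | at least 2 weeks | more than 2 weeks | Checklist |

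**Step 1: scores affected.** Whole-number CMAI scores fall into three bands.

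- 38 or less: fails both rules.
- 39, 40, 41, 42, 43 or 44: fails the synopsis and section 6.2.1, passes the checklist. That is 44 − 39 + 1 = 6 scores.
- 45 or more: passes both rules.

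**Step 2: is the difference explained elsewhere?** Section 3, Protocol Amendments, mentions new sites and the reduction of the age limit to 45. It mentions no change to the CMAI threshold, and 39 appears nowhere else as one. The conflict is in current text.

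**Step 3: would a later rule remove such a patient?** Section 6.7.4 defines the ITT population by three conditions: randomised, at least one dose taken, and valid CMAI scores at baseline and week 6 (with LOCF where needed). Eligibility is not among them. A patient with a baseline score of 39 to 44 who meets those conditions is in the primary analysis.

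**Step 4: the minor items.** A patient with an MMSE of exactly 19, or aged exactly 45, fails section 6.2.1 but passes both the synopsis and the checklist. Section 4.1 stages moderate disease as MMSE 10 to 19, which fits the ≤19 reading. On duration the checklist is stricter by one boundary value: exactly 2 weeks passes the criteria and fails the form.

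**The case against.** The strongest reply is that the form has no authority of its own. Section 6.2 makes the criteria govern, section 6.3.2 has a doctor supervise screening, and the checklist abbreviates throughout. On that view 39 is a slip on a form that section 6.2.1 overrides. Much of this stands. Nothing gives the checklist precedence, and the protocol shows what the form would permit, not that anyone scoring 39 to 44 was enrolled. The wordings on problematic agitation and on more than 2 weeks may be shorthand. A number is different: 39 cannot be an abbreviation of 45, and it is printed where the decision is recorded.

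A reader might go further and infer that milder patients would dilute the treatment difference and cost power. The documents do not support that.

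- It needs an assumed mean CMAI at screening, an assumed lowest scale score, and benefit proportional to the distance above that score. None is given.
- Sections 6.7.2 and 6.7.3 plan on a constant 6-point difference. Under a constant difference this dilution does not arise.
- The SD of 16.84 in section 6.7.2 comes from studies of agitation in dementia and is used there for the trial population. Suppose it is treated instead as the SD of a normally distributed screening population with an assumed mean of 50 to 65, cut at 45. The enrolled SD then becomes about 11.2 to 14.0, which no longer matches the SD behind the planned power.

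A reader might also infer bias between the arms. Section 6.4.2 balances allocation on severity of agitation, and section 6.7.5 uses baseline CMAI as covariate. Patients in the 39 to 44 band should be spread over both arms and adjusted for.

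**Conclusion.** The point holds as an internal contradiction in a mandatory entry criterion: 45 in both full statements of the criteria, 39 on the form that records the decision. Its size is six CMAI scores on which the two rules disagree. The consequence is a population that could differ between sites, and possible protocol deviations inside the ITT set. This rests only on the printed text and on CMAI totals being whole numbers.

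The documents do not support a count of affected patients, a loss of power or a biased comparison. They also do not prove which threshold was intended, although 45 has the better support because it stands in both places that set out the criteria. The MMSE and age differences are minor and belong to section 6.2.1, not to the checklist.

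**What to change.** Reconcile the synopsis, section 6.2.1 and the Appendix 1 checklist to one CMAI threshold. Since both criteria statements say 45 or more, change the checklist line to match, unless the sponsor confirms that 39 was intended. In that case the synopsis and section 6.2.1 are the texts to amend.

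Record any patient already enrolled with a baseline CMAI of 39 to 44 as a protocol deviation, and keep that patient in the ITT analysis.

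In the same revision:

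- change section 6.2.1 to MMSE ≤19 and age ≥45, as in the synopsis and the checklist;
- use the protocol's wording on the checklist for need for treatment and for a history of at least 2 weeks.

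The cost is a corrected one-page form and a few words in section 6.2.1. Recruitment may slow slightly if any site has been working to 39.
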